### Unexpected Adverse Events

An unexpected adverse event refers to an adverse medical event that occurs during the trial and is not explicitly mentioned in the study protocol, informed consent document, investigator's brochure, or drug usage or packaging information.

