#### Acute toxicity test in rodents (rats)

The experimental design included low, medium, and high doses of 50, 100, and 200 mg/kg administered intravenously. In the medium and high-dose groups, symptoms observed included ear reddening, reduced activity, prone posture, rapid breathing, and deep gasping; in the high-dose group, additional signs included deep gasping, arched back, and weight loss. Six out of ten rats (2 females and 4 males) died between days 1 and 6 of the experiment, and there was a decrease in body weight and food intake. Hematological analysis showed that WBC and LYM counts were reduced in the low, medium, and high-dose groups, while EOS%, RET, and RET% were elevated, demonstrating a dose-dependent relationship. Histopathological findings indicated that in the high-dose group, deceased animals exhibited dark red changes in the lungs, mild to moderate pulmonary edema, slight to moderate hemorrhage, and severe inflammation. Surviving animals showed reduced testicular volume, dark red changes at the injection site, and moderate atrophy of the seminiferous tubules. The injection site exhibited moderate inflammation accompanied by moderate ulceration, leading to the identification of the maximum tolerated dose (MTD) as 100 mg/kg.

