**Adverse events should be recorded starting from the time the subject signs the informed consent form.**

## Serious Adverse Events

Serious Adverse Event Handling Process

[figure not shown]

According to the requirements of the 2020 version of GCP, the handling process for SAEs is illustrated in the diagram.

Except for serious adverse events that do not require immediate reporting as specified in the study protocol or other documents (such as the investigator's brochure), the investigator must submit a written report of all SAEs to the sponsor within 24 hours of the event's occurrence or upon becoming aware of the event. For reports involving death, the investigator should provide the sponsor and the ethics committee with any additional necessary information, such as autopsy reports and final medical reports.

Upon receiving any safety-related information from any source, the sponsor must promptly analyze and assess it, including its severity, relevance to the investigational drug, and whether it is an anticipated event. The sponsor should report any suspected unexpected serious adverse reactions (SUSARs) to all investigators participating in the clinical trial, as well as to the regulatory authorities and health departments.

Investigators who receive safety information related to the clinical trial from the sponsor should promptly acknowledge receipt and read it. They should consider whether to make any necessary adjustments to the treatment of the subjects and communicate with the subjects as soon as possible if necessary. Additionally, they should report the SUSARs provided by the sponsor to the ethics committee.

Handling Measures: In the event of an emergency involving a patient, the investigator at the trial site should take appropriate actions based on the medication and the symptoms presented, and notify the clinical monitor of the handling results. The investigator should document the cause, date, actions taken, outcomes, and sign the SAE report form in detail.

Follow-up on Unresolved Adverse Events: All adverse events should be tracked until they are adequately resolved or the condition stabilizes.

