## Anticipated/Unexpected Adverse Events

### Anticipated Adverse Event

Based on the preclinical safety data of this drug and clinical experience with similar HDAC inhibitors, the anticipated adverse events may include:

1. Gastrointestinal abnormalities: nausea, vomiting, diarrhea, bloating, decreased appetite
2. Blood and lymphatic system abnormalities: thrombocytopenia, neutropenia, lymphopenia
3. Cardiac abnormalities: prolonged QTc interval, tachycardia, arrhythmia
4. Hepatobiliary abnormalities: elevated ALT, AST, ALP, TBIL
5. Respiratory abnormalities: dyspnea, pulmonary edema
6. Metabolic abnormalities: hyperglycemia, hyperuricemia, hypophosphatemia, hyponatremia, hypokalemia
7. Psychiatric abnormalities: insomnia
8. Neurological abnormalities: headache, dizziness
9. Vascular abnormalities: hypotension
10. Renal function abnormalities: elevated SCr
11. Infections, pneumonia
12. Fatigue, weakness, fever
13. Weight loss
14. Hemorrhage

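### Section 8.3.2 decides expectedness by mere mention, so a serious related case of a broad term listed in 8.3.1 can fall outside the SUSAR reporting duty stated in 8.2

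*Protocol*

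**What the plan says.** Three parts of protocol section 8 have to be read together.

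- **8.3.2, Unexpected Adverse Events.** The definition reads: "An unexpected adverse event refers to an adverse medical event that occurs during the trial and is not explicitly mentioned in the study protocol". The sentence then adds further documents in which a mention has the same effect: "informed consent document, investigator's brochure, or drug usage or packaging information". It gives no other condition.
- **8.3.1, Anticipated Adverse Event.** The list opens: "Based on the preclinical safety data of this drug and clinical experience with similar HDAC inhibitors, the anticipated adverse events may include". Fourteen entries follow. Among them are "Cardiac abnormalities: prolonged QTc interval, tachycardia, arrhythmia", "Respiratory abnormalities: dyspnea, pulmonary edema", infections with pneumonia, and "14. Hemorrhage". None carries a grade, a site or an outcome.
- **8.2, Serious Adverse Events.** "The sponsor should report any suspected unexpected serious adverse reactions (SUSARs) to all investigators participating in the clinical trial", and also to regulatory authorities and health departments. Investigators then pass the SUSARs they receive to the ethics committee. When the sponsor assesses incoming safety information, severity, relatedness and anticipation are three separate items.

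Section 8.2 also sends SAEs to the sponsor in writing within 24 hours, except those exempted in the protocol or other documents. Where there is a death, additional information goes to both the sponsor and the ethics committee. Section 12.2 sends important new information on the drug to the ethics committee through revised materials.

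**The concern.** Whether an event is expected decides whether a serious suspected reaction is a SUSAR, and SUSARs are the only class for which the visible text of 8.2 gives the sponsor a duty to inform regulators and health departments. A test that asks only whether a word appears somewhere treats a mild and a life-threatening form of the same term alike.

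The list in 8.3.1 is a reasonable guide to what to watch for, and 8.4 uses it in that way for risk control. It is a poor standard for expectedness. Its terms are broad, and its stated basis is animal findings and other agents. The protocol reports no human safety results for this drug. The serious harms that the sponsor can best foresee are thus the ones most easily classed as expected, before any human case has been described. That matters in a dose-escalation Phase I trial whose planned doses run from 1.2 to 15 mg/m² (15 / 1.2 = 12.5-fold, sections 3.1 and 3.2.3).

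**Working it through.** No arithmetic decides this point. The check applies the definition literally and follows the reporting duties.

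**Step 1: the test.** Under 8.3.2, an event explicitly mentioned in the protocol, consent form, brochure or drug information is expected; otherwise it is unexpected. There is no clause on severity, nature, specificity or outcome, and no document is given precedence.

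**Step 2: apply it to serious, drug-related events.**

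| Event | Named in 8.3.1 | Grade, type or site given | Unexpected under 8.3.2 | Duty to regulators stated in 8.2 as shown |
|---|---|---|---|---|
| Arrhythmia | yes | no | no | no |
| Pulmonary edema | yes | no | no | no |
| Pneumonia | yes | no | no | no |
| Hemorrhage | yes | no | no | no |

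**Step 3: does another clause repair the definition?** The sponsor's assessment in 8.2 does consider severity, but beside the question of anticipation and not as part of it. A severe case of a listed term is recorded as severe and remains anticipated.

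**Step 4: what is the list based on?** The opening of 8.3.1 gives two sources: this drug's preclinical data and clinical experience with similar agents. The preclinical source is real. In the rat acute toxicity study (1.4.2.1), high-dose animals that died had lung findings described as "mild to moderate pulmonary edema, slight to moderate hemorrhage, and severe inflammation". Slight QTc prolongation was seen in high-dose male dogs (1.4.2.4). Neither source is human experience with this drug.

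**Step 5: which routes remain for a serious, related, listed event?**

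- Written report to the sponsor within 24 hours, unless exempted (8.2).
- Prompt sponsor assessment (8.2).
- If fatal, additional information to the sponsor and the ethics committee (8.2).
- If it amounts to important new information, submission to the ethics committee (12.2). This depends on judgement, carries no deadline and does not name regulators.
- If it meets the DLT definition within 25 days of first dose, it counts in the escalation rule whether or not it is expected (3.2.4, 3.4).

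None of these is a stated duty to inform regulators or health departments of the event.

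**The case against.** The strongest reply is that this is a drafting gap with limited effect, and much of that reply stands.

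- **Onward reporting.** A reader might infer that these events would not be reported onward. The protocol does not say so. It states no duty, which is different from a bar, and the routes in step 5 remain. The SAE process diagram in 8.2 is not shown and may add routes. Section 8.2 also places SAE handling under the 2020 GCP, which is not available here.
- **Dose steps.** A reader might infer that escalation could proceed without regard to such events. It could not. Related non-hematologic toxicity of Grade 3 or higher counts as a DLT, subject to the listed exclusions, and any Grade 5 event counts. One subject per group is observed for 25 days before others enroll, and two or more DLTs send the trial back a dose group. Expectedness plays no part. The protocol gives outside bodies no routine role at each step, so it does not support a claim that they would miss the chance to question one. The limit of this reply is that DLTs are counted over 25 days, while treatment may continue beyond that.
- **Nature of the list.** Calling it a class-effect list would be inaccurate, because this drug's own animal data support part of it.
- **Breadth.** It is tempting to say that all 14 entries matter. Several are minor terms, such as insomnia, headache, dizziness, bloating and weight loss. The word explicitly also narrows the test: listing raised ALT or creatinine does not name organ failure. At the other extreme, acute myocardial infarction and stroke appear in the exclusion criteria (4.5), so a fully mechanical reading would make even those mentioned. It is unlikely that anyone intends this, and the point does not rely on it.
- **Cross-reference.** Section 8.2 does not point to 8.3.2 for the meaning of unexpected. Using that definition is an inference, though it is the only definition the protocol gives.

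These points narrow the consequence. None supplies the missing criterion or a single reference for expectedness.

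**Conclusion.** The point holds as a defect in a stated rule. Followed literally, 8.3.2 classes a serious related case of a broad term named in 8.3.1 as expected. The visible text of 8.2 then states no duty to report it to regulators or health departments.

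The consequence is confined to that stated duty. It does not extend to a loss of SAE reporting to the sponsor, a ban on onward reporting or a failure of the escalation rules. The terms that matter most are the broad ones that can be serious, chiefly arrhythmia, pulmonary edema, pneumonia or other infection, and hemorrhage. The number of reports affected cannot be calculated, because the document gives no event rates. With 7 dose groups of 3 to 6 subjects (7 × 3 = 21 to 7 × 6 = 42), it should be small.

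The conclusion rests on two assumptions: that 8.3.2 supplies the meaning of unexpected in the SUSAR duty, and that the diagram not shown does not add a reporting duty that closes the gap. The change is worth making because the protocol reports no human safety results for this drug.

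**What to change.** Amend 8.3 in three respects:

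1. State that the 8.3.1 list is for monitoring and risk control and does not determine expectedness.
2. Name one reference document for expectedness, namely the reference safety section of the investigator's brochure, and have the SUSAR duty in 8.2 refer to it.
3. Define an event as unexpected when its nature, severity, specificity or outcome is not consistent with that reference.

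The brochure is not available here. The sponsor should check whether it already has such a section and add one if it does not. The cost is a few sentences in section 8, possible alignment of the brochure, and a small number of additional expedited reports. No dose, schedule or treatment rule changes.

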## Risk Control Plan

According to Section 8.3.1, reference should be made to similar drugs and the main anticipated adverse events that may occur with this product, along with the implementation of certain risk control measures.

**Hematologic toxicity**

Hematological adverse reactions (thrombocytopenia, neutropenia, anemia) commonly occur during the early stages of treatment. Close monitoring of complete blood count (CBC) is essential, and adjustments to medication and management of related side effects should be made based on the results, ensuring safety while striving to maintain the same dosage.

For grade 1–3 neutropenia, the treatment regimen should not be changed temporarily, and granulocyte colony-stimulating factor (G-CSF) should be added. CBC should be conducted approximately every two days to monitor whether neutrophil counts recover. If there is no recovery, consideration may be given to adjusting the treatment plan. If grade 4 neutropenia persists for≥5 days, despite the addition of G-CSF, Purinostat Mesylate treatment should be permanently discontinued unless the investigator and sponsor agree to continue treatment at a reduced dose in the best interest of the subject.

Patients with multiple myeloma often present with thrombocytopenia and anemia. Close monitoring of platelet counts is essential. For grade 1–3 thrombocytopenia, it is recommended to maintain the dose under supportive treatment with recombinant human thrombopoietin injection (e.g., TPO), recombinant human interleukin-11, or platelet transfusions to prevent life-threatening or severe gastrointestinal or pulmonary bleeding. If bleeding occurs, treatment should be immediately suspended until platelet counts return to baseline levels. If the patient experiences severe anemia (e.g., hemoglobin<60 g/L), red blood cell transfusions or erythropoietin injections may be used to increase red blood cell counts.

**Liver Toxicity**

In the event of liver toxicity, additional clinical information should be collected to determine the most likely cause of the observed liver abnormalities. This includes identifying abnormalities in liver function indicators that may be due to other factors, such as concomitant medications, alcoholic and autoimmune hepatitis, tumor metastasis, disease progression, viral hepatitis, cardiovascular disease, and other causes. The following measures should be taken:

Grade 2 Toxicity

- Continue to closely monitor liver function indicators during the Purinostat Mesylate treatment cycle until they return to baseline levels.
- For patients with baseline normal liver function who experience a Grade 2 increase in ALT or AST after treatment, suspend treatment until liver function returns to Grade 1 or below. Upon resuming treatment, the dose should be reduced by one level, and the frequency of liver function monitoring should be increased.

Grade 3 Toxicity

- If ALT or AST> 5×ULN, treatment should be discontinued, and the subject should exit the study. The subject will receive a consultation from a liver disease specialist.
- Closely monitor liver function indicators. If liver function is severely impaired relative to baseline values or reaches the level of severe liver injury, the medication should be discontinued, and supportive care should be strengthened, such as bed rest and close monitoring of liver function indicators, until liver function returns to baseline levels.
- During the process of reducing the dose by one level, if Grade 2 or higher toxicity recurs, treatment should be discontinued, and the subject should exit the study.

Grade 4 Toxicity

- Treatment should be discontinued, and the subject should exit the study. The subject will receive a consultation from a liver disease specialist.

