**2）Dose Reduction and Treatment Interruption**

If a subject experiences a dose-limiting toxicity (DLT) during the single-dose or multiple-dose phases, treatment must be interrupted until the toxicity recovers to Grade 1 or below. Based on the investigator's judgment that the subject may benefit from continued treatment, the subject may resume medication.

In the continuation dosing phase, the dose may be adjusted or treatment may be interrupted according to the following rules:

| **Toxicity** | **CTCAE Grade** | **Measures** |
| --- | --- | --- |
| Nausea and vomiting | Grade 3-4 | If it occurs for the first time, consider using antiemetics for treatment and interrupt the medication until the toxicity recovers to Grade 1 or below. Continue treatment with the original dose, and it is recommended to use antiemetics as a preventive measure.  If it occurs again, interrupt the medication until recovery to Grade 1 or below, and reduce the dose to the previous level. |
| Diarrhea | Grade 3 | If it occurs for the first time, consider using antidiarrheal medication for treatment and interrupt the medication until the toxicity recovers to Grade 1 or below. Continue treatment with the original dose, and it is recommended to use antidiarrheal medication as a preventive measure.  If it occurs again, interrupt the medication until recovery to Grade 1 or below, and when resuming treatment, reduce the dose to the previous level. |
|  | Grade 4 | If it occurs for the first time, consider using antidiarrheal medication for treatment and interrupt the medication until the toxicity recovers to Grade 1 or below. Adjust the dose to the previous level for treatment, and it is recommended to use antidiarrheal medication as a preventive measure.  If it occurs again, discontinue treatment and withdraw from the study. |
| Neutropenia | Grade 3 | ANC: 0.75 - 1.0 × 10^9^ /L, maintain the current dose and continue treatment. ANC: 0.5 - 0.75 × 10^9^ /L, interrupt treatment until ANC recovers to 1.0 × 10^9^ /L, then continue treatment at the original dose. |
| Febrile neutropenia | Grade 3 | Interrupt treatment until ANC recovers to 1.0 × 10^9 /L; when resuming treatment, reduce the dose to the previous level. |
| Thrombocytopenia | Grade 3 | Maintain the current dose of treatment and monitor platelet counts weekly |

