|  | Grade 3-4 | Grade 3 thrombocytopenia with bleeding: interrupt treatment until PLT recovers to 50 × 10^9^ /L; when resuming treatment, reduce the dose to the previous level and monitor platelet counts weekly.  Grade 4 thrombocytopenia: interrupt treatment until PLT recovers to 50 × 10^9^ /L; when resuming treatment, reduce the dose to the previous level and monitor platelet counts weekly. |
| Anemia | Grade 3 | Interrupt treatment until Hb recovers to 10 g/dL; when resuming treatment, reduce the dose to the previous level. |
| QTc interval prolongation | Grade 2 | If it occurs for the first time: interrupt treatment until QTc < 450 ms; when resuming treatment, reduce the dose to the previous level.  If it occurs again: discontinue treatment and withdraw from the study. |
| Neurotoxicity | Grade 2 | If it occurs for the first time: interrupt treatment until the toxicity recovers to Grade 1 or below; when resuming treatment, reduce the dose to the previous level.  If it occurs again: discontinue treatment and withdraw from the study. |
| Liver function (elevated ALT and AST levels) | Grade 2 | Baseline normal, with Grade 2 elevation of ALT or AST occurring after treatment.  If it occurs for the first time: interrupt medication until toxicity recovers to Grade 1 or below; when resuming medication, reduce the dose by one level and increase the frequency of liver function monitoring.  If it occurs again: discontinue treatment and withdraw from the study. |
|  | Grade 3 | For patients with normal baseline, if Grade 3 toxicity occurs with ALT or AST > 8 × ULN, discontinue treatment and withdraw from the study.  For patients with Grade 1 baseline, if Grade 3 toxicity occurs with ALT or AST > 8 × ULN, consider discontinuing treatment and withdrawing from the study.  For patients with normal baseline or Grade 1 baseline, if Grade 3 toxicity occurs for the first time with 5 × ULN < ALT or AST < 8 × ULN, interrupt medication until toxicity recovers to Grade 1 or below; when resuming medication, reduce the dose by one level and increase the frequency of liver function monitoring. If it occurs again, discontinue treatment and withdraw from the study. |
|  | Grade 4 | Discontinue treatment and withdraw from the study. |
| Others | Grade 2-3 | For relapsedGrade 2-3 toxicities, except for alopecia and fatigue, treatment must be interrupted until the toxicity recovers to Grade 1 or below; when resuming treatment, reduce the dose to the previous level. |

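### Grade 3 ALT/AST in the continuation phase: Section 3.2.5 has the patient resume one dose level lower, while Section 8.4 takes the same patient off study

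*Protocol*

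**What the plan says.** Section 3.2.5, under Dose Reduction and Treatment Interruption, contains a toxicity table introduced by "In the continuation dosing phase, the dose may be adjusted or treatment may be interrupted according to the following rules". Its Grade 3 ALT/AST row applies to patients with a normal or Grade 1 baseline and reads in part: "if Grade 3 toxicity occurs for the first time with 5 × ULN < ALT or AST < 8 × ULN, interrupt medication". The hold lasts until Grade 1 or below, and then "when resuming medication, reduce the dose by one level and increase the frequency of liver function monitoring". Withdrawal follows only on a repeat. The Grade 2 ALT/AST row words this as "If it occurs again: discontinue treatment and withdraw from the study", and the Grade 3 row carries the same instruction. Above 8 × ULN, the row orders withdrawal for a normal baseline but asks only that it be considered for a Grade 1 baseline.

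Section 8.4 (Risk Control Plan, Liver Toxicity) sets its own Grade 3 rule: "If ALT or AST> 5×ULN, treatment should be discontinued, and the subject should exit the study". It has no qualifier for first occurrence, baseline, study phase or an upper limit. A later bullet in the same list adds: "During the process of reducing the dose by one level, if Grade 2 or higher toxicity recurs, treatment should be discontinued".

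For the single- and multiple-dose phases, Section 3.2.5 has different text. After a DLT, dosing stops until Grade 1 or below, and if the investigator judges that "the subject may benefit from continued treatment, the subject may resume medication".

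**The concern.** An investigator facing a first ALT of, say, 6 × ULN in the continuation phase is told by one section to hold and resume at a reduced dose, and by the other to end treatment and participation. Tolerability and safety are the primary purpose of the trial (Section 2.1), and raised ALT and AST are listed as anticipated events (Section 8.3.1).

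The two possible errors run in opposite directions. A patient may be re-exposed when the sponsor meant the patient to leave, or may lose a treatment that is helping when the sponsor meant a dose reduction. Cumulative exposure and the count of discontinuations for toxicity would also depend on which section was read.

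**Working it through.** No figure in the plan needs reproducing. The check sets the two rules side by side, asks who falls under both, and sizes the difference per patient.

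**1. The two rules compared (continuation phase)**

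| ALT/AST event | Section 3.2.5 | Section 8.4 | Result |
| --- | --- | --- | --- |
| Grade 2, normal baseline, first | Hold, resume one level lower | Hold, resume one level lower | Agree |
| Grade 3, above 5 and below 8 × ULN, normal or Grade 1 baseline, first | Hold, resume one level lower | Discontinue, exit | Contradict |
| Grade 3, exactly 8 × ULN | No rule | Discontinue, exit | Gap in 3.2.5 |
| Grade 3, above 8 × ULN, normal baseline | Discontinue, withdraw | Discontinue, exit | Agree |
| Grade 3, above 8 × ULN, Grade 1 baseline | Consider discontinuing | Discontinue, exit | Conflict |
| Recurrence after a reduction for Grade 3 | Withdraw if the Grade 3 event recurs | Stop at any recurrence of Grade 2 or higher | Differ |
| Grade 4 | Discontinue, withdraw | Discontinue, exit | Agree |

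The Grade 2 agreement is close in wording as well as substance: Section 8.4 says "Upon resuming treatment, the dose should be reduced by one level, and the frequency of liver function monitoring should be increased". Its diarrhea and nausea/vomiting rules also follow the Section 3.2.5 table. For these toxicities Section 8.4 restates the same scheme, so the Grade 3 liver difference looks like a drafting error.

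**2. Can the Section 8.4 bullet mean a temporary hold?** No. It adds study exit in the same sentence, and for Grade 2 the section uses a different verb (suspend) for a hold.

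**3. Who falls under both rules?** Section 4.4 requires ALT and AST ≤ 1.5 × ULN at entry. Appendix 14.3 gives Grade 1 as above ULN to 2.5 × ULN. Since 1.5 < 2.5, every eligible entry value is normal or Grade 1. The hold-and-resume rule therefore covers every eligible patient who has a first elevation between 5 and 8 × ULN.

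**4. Size per patient.** One level lower as a share of the current dose, from Table 7:
- 1.2/2.4 = 50%
- 2.4/4.0 = 60%
- 4.0/6.0 = 66.7%
- 6.0/8.4 = 71.4%
- 8.4/11.2 = 75%
- 11.2/15 = 74.7%
- any further level, at 33% steps: 1/1.33 = 75.2%

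Section 3.2.5 thus gives re-exposure at about 50% to 75% of the causative dose, and Section 8.4 gives zero. At 1.2 mg/m² there is no lower level, so the Section 3.2.5 reduction cannot be carried out.

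**5. Does D1–D25 matter?** A drug-related Grade 3 liver event with a baseline of Grade 1 or below is a DLT under Section 3.4. Such a patient is evaluable under Section 3.2.4, having had a DLT after at least one dose. Whether dosing later resumes does not change that count.

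**The case against.** The strongest reply is that the conflict is narrower than it looks.

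- **Permissive lead-in.** The sentence introducing the Section 3.2.5 table says that the dose *may* be adjusted. The liver row itself is imperative, however, and even on a permissive reading it allows a resumption that Section 8.4 forbids.
- **A cautious course is open.** Section 4.6 lets the investigator end participation for other reasons, and Section 8.1.4 leaves interruption and dose adjustment to clinical judgement. Stopping above 5 × ULN can therefore be defended, and the sharper problem is resumption. This stands. It also makes the conflict above 8 × ULN with a Grade 1 baseline the milder of the two, since an investigator who stops there satisfies both sections. It does not say which rule the sponsor intends.
- **Limited reach.** The trial is single-centre, both rules stop dosing at once, and they part only over re-exposure after recovery, at a lower dose and with closer monitoring. This also stands. A single centre does not prevent different decisions for different patients.
- **Section 8.4 as the stricter rule.** A reader might infer that it simply prevails. No text says so, and it would leave the 8 × ULN threshold and the resume rule in Section 3.2.5 without effect.
- **Section 8.4's recurrence bullet.** A reader might infer from its mention of a dose reduction that Section 8.4 itself allows continuation after Grade 3. The bullet fits a reduction after Grade 2 equally well, so it settles nothing.

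**Conclusion.** The protocol is wrong as written on this point. For a first ALT/AST elevation between 5 and 8 × ULN in the continuation phase, the two sections give instructions that cannot both be followed. Above 8 × ULN with a Grade 1 baseline, one section leaves to judgement what the other requires. The per-patient difference is resumption at about 50% to 75% of the causative dose against permanent exit.

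Two stronger readings are not supported. A reader might infer that dose escalation or the MTD is compromised. The D1–D25 DLT count does not depend on what happens after the event, and in that period Section 3.2.5 only permits resumption, so following Section 8.4 there breaches nothing. A reader might also want a number or probability of affected patients. The protocol gives neither the incidence of such elevations nor the number of patients expected in the continuation phase, so any figure would rest wholly on assumption. The conclusion needs none: two incompatible stopping rules for an anticipated toxicity should be reconciled at any incidence.

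**What to change.** Make the ALT/AST rows of the Section 3.2.5 table the single dose-modification rule. The medical team should settle there:
- one action for above 5 and below 8 × ULN;
- one action for 8 × ULN and above, stated for each baseline, which also assigns the value 8 itself;
- one recurrence trigger after a reduction, either Grade 2 or Grade 3;
- the action for a patient already at 1.2 mg/m².

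In Section 8.4, replace only the instruction to exit above 5 × ULN and the recurrence bullet with a cross-reference to Section 3.2.5. Keep the liver-specialist consultation, the stop for severe liver injury and the supportive-care text. The ALT/AST rows of Section 3.2.5 contain none of these, so replacing the whole Grade 3 list would lose them for Grade 3 events.

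The cost is a few clinical decisions and a wording amendment, approved by the sponsor, the investigator and the ethics committee as Section 11.1 requires. It needs no added visits, tests or patients.
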